## Abstract

**Background:**

ChAdOx-1s, CoronaVac, BBIBP-CorV, mRNA-1273, and BNT162b2 are the five common COVID-19 vaccines used in Jakarta. Randomized controlled trials have provided robust evidence of the safety and efficacy profile of these vaccines, but their real-world vaccine effectiveness against symptomatic COVID-19 and deaths in communities with social inequalities and health care constraints remains unclear.

**Objective:**

This study aims to evaluate the real-world effectiveness of these COVID-19 vaccines during the waves associated with the Delta and Omicron variants by analyzing existing electronic health care sources.

**Methods:**

A population-based study with a test-negative case-control design will be used to evaluate COVID-19 vaccine effectiveness in Jakarta, focusing on the Delta and Omicron waves. It includes adults 18 years and older who underwent reverse transcription polymerase chain reaction testing for symptomatic COVID-19, classifying them as cases or controls based on their test results. The analysis will consider multiple COVID-19 vaccines introduced during these periods, with participants categorized by vaccination status. Several potential confounders will be assessed, including demographic factors and comorbidities. Data will be linked from various health datasets, and statistical analyses will be performed to determine vaccine effectiveness and potential waning immunity over time. After data linkage, patients’ identities will be encrypted.

**Results:**

The research, funded from 2022 to 2024, involved proposal preparation and ethical review in 2023 and enrollment from early 2024 to July 2024, resulting in about 4 million linked data points. Data analysis is ongoing, with initial results expected for publication in early 2025.

**Conclusions:**

This study will be the first to evaluate the effectiveness of different types of COVID-19 vaccines (inactivated, viral-vector, and mRNA) used in Jakarta during the pandemic, providing valuable scientific evidence to inform future vaccination strategies in the country.

**International Registered Report Identifier (IRRID):**

DERR1-10.2196/56519

## Introduction

### Background

Since its emergence in December 2019, SARS-CoV-2, which is the virus that causes COVID-19, has been continuously spreading worldwide [1]. As of November 12, 2021, this pandemic has caused more than 250 million cases and more than 5 million deaths over the previous 2 years [2]. Vaccination programs are one of the most successful public health interventions that primarily aim to develop herd immunity and protection against pathogens. To date, the World Health Organization has approved 8 COVID-19 vaccines that are efficacious in preventing infection, reducing the level of severity and the number of deaths due to SARS-CoV-2 infection [3]. However, most data were generated from clinical trial studies that were different from a real-world setting due to their well-controlled nature [4]. Furthermore, real-world vaccine effectiveness (VE) studies were mostly conducted in high-income nations, and few studies came from low- and middle-income countries, even though these countries might have unique social and economic characteristics that not only affect vaccination acceptance but also disease outcomes [5]. A previous study has reported the association of living in an impoverished neighborhood with an increased risk for mortality even after COVID-19 vaccination [6]. Therefore, studies investigating how these COVID-19 vaccines might perform in real-world settings where social inequalities exist are still essential for informing policies and strategies to improve disease outcomes in future pandemics, especially in societies with health care system constraints [7]. This study aims to evaluate COVID-19 VE against symptomatic and fatal SARS-CoV-2 infection during the Delta and Omicron waves in Jakarta, where income inequality and socioeconomic segregation have become a common phenomenon [8].

### Study Objectives

The primary objective is to study real-world VE against symptomatic COVID-19 (mild, moderate, and severe).

The following secondary objectives were also explored:

Real-world VE against mortality 30 days after the first positive COVID-19 resultReal-world VE based on vaccination status at the time of the reverse transcription polymerase chain reaction (RT-PCR) testReal-world VE based on the time since receipt of the last vaccine dosage

## Methods

### Study Design and Setting

This population-based study adopts a test-negative case-control design to analyze COVID-19 VE against symptomatic and fatal SARS-CoV-2 infection from available health care datasets in the Special Capital Region of Jakarta, one of the provinces with the highest population density (15,900 people per km^2^ in 2020) and case rate per population relative to other regions in Indonesia [9]. Despite its robust development and economic growth, the contrast between rich and poor neighborhoods was highly prevalent in many parts of Jakarta’s districts [8,10].

This study will estimate VE against COVID-19 during the period of interest, which were the COVID-19 waves associated with the Delta and Omicron variants, from June 1 to August 31, 2021, and January 1 to April 2, 2022, respectively. Within each of these periods, a cycle of sustained upward and downward trends of the test positivity rate was observed [11-15] (Figure 1). Furthermore, the Delta and Omicron variants were estimated to be responsible for around 90% of SARS-CoV-2 infections in Jakarta during these two periods [14,16].

**Figure 1 figure1:**
[figure not shown]
Trend of the national COVID-19 positivity rate in Indonesia from 2021 to 2022. This modified image is cited from Our World in Data.

During the Delta and Omicron periods, several brands of COVID-19 vaccines were introduced in Jakarta for vaccine rollout, such as AstraZeneca, SinoVac-CoronaVac Biofarma, Covovax-Novovax, Indovax, Johnson & Johnson, Moderna, Sinopharm BBIBP, and Pfizer (Table S1 in Multimedia Appendix 1) [17]. Among these COVID-19 vaccines, Coronavac-Sinovac was the earliest COVID-19 vaccine to be introduced in January 2021 and used for mass vaccinations of doses 1 and 2, followed by AstraZeneca, Sinopharm, Pfizer, and Moderna in August 2021 [18,19]. Booster vaccinations 6 months after the 2-dose primary vaccination with Moderna and Pfizer vaccines were initially introduced to health care workers in July 2021, followed by the approval of the AstraZeneca vaccine as a booster in the national vaccination program in January 2022 [20,21]. To expedite the booster vaccination coverage, the timeline for booster administration was shortened to 3 months after the 2-dose primary vaccination, and additional inactivated COVID-19 vaccines, such as SinoVac and Sinopharm, were included in the national booster program [22]. Different from Pfizer, Moderna, and AstraZeneca, these inactivated COVID-19 vaccines were only approved as boosters for patients who received similar vaccine platform for their primary vaccination regimen [23]. Until the end of the Omicron period, all of the distributed COVID-19 vaccines in Jakarta were developed from the ancestral strain of SARS-CoV-2.

### Study Participants

The study will include people 18 years or older who domiciled in Jakarta and underwent an RT-PCR test for SARS-CoV-2 infection due to symptoms of influenza-like illnesses within 10 days of the test date. Although people may have more than one RT-PCR result during the period of interest, this study will only account for the first positive or negative result per person as the index test date for each of the COVID-19 waves. People who had at least one sample with a positive SARS-CoV-2 RT-PCR result during the period of interest will be classified as cases, while people with a negative SARS-CoV-2 RT-PCR without any positive results over the period of interest will be classified as controls.

People with a positive RT-PCR test result within 90 days of the preceding index test date, with inconclusive RT-PCR results, who received different vaccines for dose 1 and dose 2 or a heterologous primary vaccine series, or who had a time interval between dose 1 and dose 2 that was less than the government recommendation (<21 days for Pfizer and Sinopharm, <28 days for CoronaVac and Moderna, and <12 weeks AstraZeneca) will be excluded from the analysis. We will also exclude people with incomplete vaccination records, such as people who declared receiving 2 vaccine doses without being able to verify the previous dose.

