### Data Sources

This study will analyze the final datasets derived from the integration of several datasets provided by the Jakarta Provincial Health Office, Ministry of Health, and Social Security Agency on Health after April 2022 (Table 1). Variables such as ID number and date of birth will be used for the dataset linkage (Figure 2). From the New All Records (NAR) and Suspect and Probable (SUSPROB) datasets, symptomatic people with a positive or negative first RT-PCR test result within each of the periods of interest will be identified as cases or controls. Furthermore, people identified as cases will be linked to the entries in the REV POS dataset to extract the outcome of their disease course (Figure 2). People with incomplete data for ID number, date of birth, gender, swab collection date, PCR test result, domicile address, outcome, and date of death (if the case ends in death) will be excluded from further data linkage.

**Table 1 table1:** List source for merged datasets.

Name	Developer	Description	Variable identified
NAR^a^	Ministry of Health Republic of Indonesia	Record of all RT-PCR^b^ SARS-CoV-2 tests carried out by affiliated laboratories	Name ID number Date of birth Sex (male, female) Comorbidity Domicile address Laboratory name Reason for testing Swab collection date RT-PCR result confirmation date RT-PCR testing result
SUSPROB^c^	Jakarta Provincial Health Office	Record and follow-ups of all people with influenza-like illness or probable COVID-19	Name ID number Date of birth Sex (male, female) Comorbidity Domicile address Presence of influenza-like illness (fever, chill, cough, etc) Date of symptom onset Travel history Plan swab testing date Swab collection date RT-PCR testing result
REV POS	Jakarta Provincial Health Office	Records and follow-ups on all positive cases in Jakarta	Name ID number Date of birth Sex (male, female) Comorbidity Domicile address Date of swab collection Case severity (asymptomatic, mild, moderate, severe) Outcome (survived or death) Date of death
PCARE^d^ Vaksin	Social Security Agency on Health Indonesia (BPJS Kesehatan)	Record of all administered COVID-19 vaccines and their recipients	Name ID number Date of birth Sex (male, female) Domicile address Occupation or vaccination batch group (health workers, government officials, elderly, children, civilians) Name of health care facility/vaccination center Vaccination date Vaccination ticket number Vaccination dose Vaccine name Vaccine batch/lot number

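### A person who tests negative and later positive in the same wave is classified differently in two sections, and the never-positive control rule looks ahead and raises VE

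*Protocol article*

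**What the plan says.** Study Participants defines cases by any positive in the wave: "People who had at least one sample with a positive SARS-CoV-2 RT-PCR result during the period of interest will be classified as cases". Controls must stay negative throughout: "people with a negative SARS-CoV-2 RT-PCR without any positive results over the period of interest will be classified as controls". On dating, it says that "this study will only account for the first positive or negative result per person as the index test date", separately for each wave.

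Data Sources gives another rule: "symptomatic people with a positive or negative first RT-PCR test result within each of the periods of interest will be identified as cases or controls".

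The exclusions in Study Participants begin with "People with a positive RT-PCR test result within 90 days of the preceding index test date". They do not say whether that preceding index test has to be a positive one.

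Study Variables reads vaccination status from the last dose before the index test. It defines unvaccinated as having no vaccination entry by the end of the period.

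Data Sources also lists fields that must be complete. The list ends: "domicile address, outcome, and date of death (if the case ends in death) will be excluded from further data linkage". In Table 1 the outcome field appears only in REV POS, which records positive cases.

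**The concern.** These sentences build the primary dataset, and they disagree about a recognisable group: people with a negative test followed by a positive one in the same wave. Two analysts working from the two sections would produce different cases and different controls.

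The control rule also depends on the future. A person tested negative in week 1 qualifies only by avoiding a positive for the rest of the wave. If the vaccine works, those who fail are disproportionately unvaccinated. Removing them raises the vaccination odds among controls and so raises VE. Matching on calendar week does not undo this, and Table 3 does not list it among the potential biases.

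If the index date is the first test of either result, a case could be dated at an earlier negative. Vaccination status, time since dose and matching week would then be read at the wrong date.

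The completeness filter on outcome acts on cases alone, although the primary endpoint does not need survival status.

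**Working it through.** **1. Wave length.** June 1 to August 31, 2021: 30+31+31 = 92 days. January 1 to April 2, 2022: 31+28+31+2 = 92 days. Two tests in one wave are at most 91 days apart, so almost every negative-then-positive pair lies within 90 days.

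**2. One person, three answers.** Take someone negative in June and positive in August.

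| Rule | Status |
|---|---|
| Study Participants, case and control definitions | Case |
| Data Sources, first result | Control |
| 90-day exclusion, if the earlier negative is the preceding index test | Excluded |

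No section says which rule governs.

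**3. The plan's precision, as a yardstick.** Sample Size asks for ±5% and arrives at about 5000 cases and 10,000 controls. With n = z²[1/(p₁q₁) + 1/(2p₀q₀)]/(d/OR)², q = 1−p, VE 50%, p₀ = 0.20, p₁ = 0.2×0.5/(0.8+0.1) = 0.111 and d = 0.05: 3.84×(10.125+3.125)/0.01 ≈ 5,090 cases, or 15,270 people at 1:2. This agrees with the plan, so ±5 is a half-width in VE points.

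**4. Bias from never-positive controls.** Let r be the share of unvaccinated test-negatives who later test positive in the wave, and r×OR the share among the vaccinated, with OR = 1−VE. The fractions kept as controls are 1−r and 1−r×OR, so

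OR_obs = OR × (1−r)/(1−r×OR).

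The document does not give r; the range is assumed.

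| r | True VE 50% | True VE 90% |
|---|---|---|
| 1% | 50.3 | 90.1 |
| 5% | 51.3 | – |
| 10% | 52.6 | 90.9 |
| 20% | 55.6 | – |
| 30% | 58.8 | 92.8 |

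Example: 0.5×0.90/0.95 = 0.474, so VE = 52.6%. The shift reaches 5 points at r ≈ 18% for VE 50% (0.05/0.275) and at r ≈ 53% for VE 90% (0.05/0.095).

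**5. Simulation of a 92-day wave, stratified by week.** Assumed: coverage 60%, wave incidence 5%–30% in the unvaccinated, 0%–15% false negatives within the same illness, true VE 50%, 70% or 90%; 54 scenarios. The comparator took controls not yet positive when tested. It returned the true VE within Monte Carlo error (about 49 to 51 for a true 50).

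- Study Participants rule, under either reading of the index date: above the comparator in all 54 scenarios, by 0.1 to 4.4 points.
- Excluding negative-then-positive people: nearly the same upward shift.
- Data Sources rule: no material bias when later positives are new infections. With false negatives the bias is downward, at most about 10 points (49.8 to 39.8 at VE 50%, incidence 30%, 15% false negatives).

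**6. Index date.** The phrase "first positive or negative result per person as the index test date" can mean first positive for cases and first negative for controls, or first test of either result. On the second reading, someone first vaccinated between the two tests has no dose before the index date. That person is not unvaccinated either, because an entry exists by the end of the period. No exposure group fits.

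**7. Outcome filter.** Read literally, it removes every control, since controls have no REV POS record. Read sensibly, it screens cases only. The OR is multiplied by (share of vaccinated cases kept)/(share of unvaccinated cases kept). With assumed missingness of 15% (vaccinated) and 5% (unvaccinated): 0.5×0.85/0.95 = 0.447, VE 55.3%. With 5% and 10%: 0.5×0.95/0.90 = 0.528, VE 47.2%. With equal missingness there is no bias.

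**The case against.** The strongest reply is that this is a clarification and the bias is modest. The document does not give r. Up to r = 10% the shift is about 0 to 3 points, it is smaller still at high VE, and no simulated scenario reached 5 points, because controls tested late in a wave have little time left to turn positive. Dropping a negative from the same illness as a positive is also sound, since it corrects outcome misclassification. All of this stands. It limits the size of the bias but does not settle which rule applies.

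Four stronger readings are tempting, and the document does not support them:

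- *The conflict as a whole inflates VE.* Only the never-positive rule, or outright exclusion, does. The first-result rule is neutral or errs downward, possibly by more.
- *Case status certainly depends on later events.* That needs the first-test-of-either-result reading. If cases are dated at their first positive, only control status looks ahead.
- *Doses taken between the tests move breakthrough cases into the unvaccinated group.* The end-of-period definition of unvaccinated rules this out; such people fall into no group.
- *The bias is as large as the planned ±5 points.* That holds only for r of roughly 18% or more at VE 50%, or for strongly differential missingness of outcome.

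**Conclusion.** The concern holds in this form. The two sections contradict each other on who is a case and who is a control, and the 90-day exclusion may add a third answer. The never-positive control rule is wrong as written: it conditions on the future and overstates VE whenever VE is above zero. At a true VE of 50% the overstatement is 0.3 points at r=1%, 2.6 at r=10% and 8.8 at r=30%; at a true VE of 90% it is at most 2.8 points over that range. These sizes rest on assumed r and on the risk of a later positive scaling with 1−VE.

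The dating of cases is ambiguous, and on one reading it leaves some people without an exposure group. The outcome filter is a separate, smaller defect: its bias may go either way and is zero if missingness is unrelated to vaccination. Since the Results section reports that analysis is under way, the rule should be settled before primary estimates are issued.

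**What to change.** Use one rule, worded identically in Study Participants and Data Sources:

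- **Case:** first symptomatic positive in the wave; the index date is that specimen's date.
- **Control:** first symptomatic negative in the wave; the index date is that specimen's date. Drop it only for a positive in the 90 days before, or within a short fixed window after (for example 14 days, to catch the same illness).
- **Later positive outside that window:** counts as a case on its own date, and the earlier negative stays a control.
- **90-day exclusion:** state that the preceding index test means a positive test.
- **Outcome and date of death:** require them only for the mortality analysis.

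The cost is a rewording and a dataset rebuild. Some people will contribute both a control and a case record, which person-clustered standard errors can handle. The short window still looks ahead, but over about 14 days instead of the rest of a 92-day wave. The rebuilt data would also show how many people test negative and then positive, by vaccination status, so r need no longer be assumed.

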### Study Variables

The primary outcome in this study is symptomatic SARS-CoV-2 infection, defined as a positive RT-PCR test within 10 days from the onset of influenza-like illness. The secondary outcome in this study is fatal SARS-CoV-2 infection, defined as death within 30 days after a positive RT-PCR test result [24]. Meanwhile, the primary exposure in this study was vaccination status, which can be classified as unvaccinated, dose 1 or partial vaccination, dose 2 or primary vaccination, and booster dose. People without any vaccination entries after data linkage with the PCARE Vaksin dataset at the end of each period of interest will be classified as unvaccinated persons. For vaccinated people, we will only consider the last vaccination data entry that happened before the patients’ index RT-PCR test date.

Several covariates should be assessed as potential confounders in the study, such as age in years at the index test date, gender, calendar week of the RT-PCR collection during the period of interest, living in impoverished neighborhoods, presence of any comorbidities, occupation, and reinfection status. The calendar week of the RT-PCR collection during the period of interest will be presented as a whole number starting from week 1 as the start of the period of interest. Living in an impoverished neighborhood will be presented as a dichotomous variable. People will be classified as living in an impoverished neighborhood if their neighborhood number at the subdistrict level is listed as one of the impoverished neighborhoods in the 2018 Jakarta Governor’s regulation concerning improving the quality of settlements in residential areas. Occupation will be presented as categorical variables that consist of health care worker, public or government official, and civilian. Reinfection or people with previous SARS-CoV-2 infections will be presented as a dichotomous variable. People with a previous positive RT-PCR SARS-CoV-2 result that occurred more than 90 days after the current case will be classified as people with a previous SARS-CoV-2 infection [25].

To control for unmeasured confounders [26], such as societal preventive measures or the changing dynamic of the viral transmission within the community, this study will match each case with a control using a ratio of 1:2 by matching for age within 10 years of the case’s age, gender, and the calendar week of the RT-PCR collection during the period of interest. The matching procedure will be assessed with standardized mean differences, with values less than 0.1 indicating sufficient matching [27,28].

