**Figure 2 figure2:**
[figure not shown]
Study workflow. PCare: Primary Care.

People with data linked to the entries within the Primary Care (PCARE) Vaksin dataset will be classified as vaccinated people (Figure 2). To avoid misclassification of foreigners as unvaccinated people, the study will only use entries with national identity card numbers as ID numbers from each of the study datasets. Vaccinated people with incomplete data on vaccination date and vaccine name will be excluded from the final dataset (Table S2 in Multimedia Appendix 1). From the final dataset, a subset of data containing the matched cases and controls will be created (Table S3 in Multimedia Appendix 1).

As genomic testing was not routinely performed in Indonesia, no data linkage will be performed on the variant dataset. In contrast, the variant dataset, which consisted of the genomic test result of the randomly sampled specimen from the population, will be used to confirm the dominant SARS-CoV-2 variant in Jakarta during each period of interest.

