### Statistical Analysis

We adopted our VE analysis from the Interim Guidance of Evaluation of COVID-19 Vaccine Effectiveness by the World Health Organization, where the final estimate of absolute VE (aVE) will be determined by calculating the adjusted odds ratio (aOR) for vaccination using the formula aVE = (1 – aOR) × 100% [24]. Unconditional multivariable logistic regression will be used to analyze the aOR of having symptomatic and fatal SARS-CoV-2 infection between the unvaccinated and vaccinated participants. We will perform separate analyses for the Delta- and Omicron-dominant periods. Furthermore, within each period, we will also analyze each vaccinated person separately by their vaccine brand or platform and vaccination doses, such as dose 1, dose 2, or booster. For the main aVE analyses, we will include only vaccinated people with the last dose 1 or dose 2 vaccination date within 14-90 days or with the last booster dose within 7-90 days before their index test date and compare them to the unvaccinated people.

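### Unvaccinated status is dated to the end of the wave instead of the index test, so people first dosed after their test leave the reference group; this inflates VE against death and can shift VE against symptomatic infection either way

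*Protocol article*

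**What the plan says.** The protocol article dates vaccination status in three ways.

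- **Study Variables, unvaccinated.** The class consists of "People without any vaccination entries after data linkage with the PCARE Vaksin dataset at the end of each period of interest". The reference date is the last day of the wave.
- **Study Variables, vaccinated.** For these people "we will only consider the last vaccination data entry that happened before" the index test. The reference date is the test.
- **Data Sources, text below Figure 2.** "People with data linked to the entries within the Primary Care (PCARE) Vaksin dataset will be classified as vaccinated people". No date condition is attached.

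The Study Objectives list VE by "vaccination status at the time of the reverse transcription polymerase chain reaction (RT-PCR"), which again points to the test date. The waves run "from June 1 to August 31, 2021, and January 1 to April 2, 2022, respectively". Absolute VE is estimated "using the formula aVE = (1 – aOR) × 100"%, with unvaccinated people as the comparator in the main analyses and in the time-since-dose subgroups (Statistical Analysis). The fatal outcome is "death within 30 days after a positive RT-PCR test result".

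**The concern.** Take a person with no dose at the index test who receives a first dose three weeks later, still within the wave. By the end of the wave there is a register entry, so the person is not unvaccinated. There is no dose before the test, so the person is not in the dose 1, dose 2 or booster class either. Read as written, this person enters no contrast.

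What is lost is more than sample size. The reference group is selected on something that happens after the test result is known, and the result may influence it. A person who dies soon after a positive test can hardly receive a first dose later, so unvaccinated deaths stay in the reference group while some of their unvaccinated comparators are removed. For symptomatic infection the same distortion arises if recently infected people start vaccination less often, or later, than people who tested negative. The reference group serves every absolute VE estimate in both waves, including the primary objective.

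**Working it through.** **The plan's own figure.** The Sample Size section gives about 5000 cases and 10,000 controls for a precision of ±5%. The least favourable end of its ranges is VE 50% with coverage 20%:

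- p0 = 0.20, OR = 0.5, p1 = 0.5 × 0.20/(0.80 + 0.5 × 0.20) = 0.111
- n_cases = 1.96² × [1/(p1q1) + 1/(2p0q0)]/(0.05/0.5)² = 3.84 × (10.125 + 3.125)/0.01 ≈ 5,090

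With two controls per case the total is about 15,270, which agrees with the stated size. So ±5% is a half-width of 5 VE points, a fair yardstick for the shifts below.

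**The distortion.** Let a and b be vaccinated cases and controls, and c and d the cases and controls unvaccinated at the test. Then OR = ad/(bc). Let f_case and f_control be the shares of c and d first dosed between the test and the end of the wave. The rule leaves c(1 − f_case) and d(1 − f_control), while a and b are unchanged:

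OR_observed = OR_true × (1 − f_control)/(1 − f_case)

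This is exact for the crude odds ratio, and within any stratum. Each wave lasts 92 days counting both end dates, so that is the longest window for a later first dose.

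**Inputs not in the article.** It gives no f for cases or controls. All values below are assumptions.

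| Outcome | f_control / f_case | Multiplier | True 50% reads | True 70% reads | True 90% reads |
|---|---|---|---|---|---|
| Symptomatic | 20% / 5% | 0.80/0.95 = 0.842 | 57.9% | 74.7% | 91.6% |
| Symptomatic | 40% / 10% | 0.60/0.90 = 0.667 | 66.7% | 80.0% | 93.3% |
| Symptomatic | equal | 1 | 50% | 70% | 90% |
| Symptomatic | 20% / 30% | 0.80/0.70 = 1.143 | 42.9% | 65.7% | 88.6% |
| Death | 20% / 0% | 0.80 | 60% | 76% | 92% |
| Death | 40% / 0% | 0.60 | 70% | 82% | 94% |

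In the death rows, f_control means f in whichever group the deaths are compared with.

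**Against 5 points.** The shift is (1 − VE) × (1 − multiplier). It exceeds 0.05 when the multiplier is below 0.90 at VE 50%, below 0.833 at 70% and below 0.50 at 90%. The symptomatic scenario 20%/5% passes 5 points at VE 50% but not at 70% (4.7 points), and no scenario in the table does so at 90%.

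**How f could reach such values.** Assume tests spread evenly over 92 days and a first-dose uptake of 20% per month among the unvaccinated. Then f_control = 27.6%. If cases wait 0, 14 or 30 days before becoming as likely to start, f_case = 27.6%, 20.5% or 13.4%, and a true VE of 50% reads 50%, 54.5% or 58.2%. For death it reads 63.8%.

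**Relative VE.** The formula in Statistical Analysis reduces to 1 − OR_booster/OR_2dose. Both odds ratios carry the same multiplier, so it cancels.

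**The case against.** The strongest reply is that the exclusion is inferred. People first dosed after their test are not in the article's exclusion lists. The end-of-period phrase could simply be the register cut-off for the linkage run, which is needed because the data were supplied after April 2022. The other dated exposure rules, namely the post-dose windows, the time-since-dose table and the objective, all look back from the index test. The linkage sentence below Figure 2 describes a workflow and may not be meant as a timing rule. This makes it likely that test-date status was intended, but it does not repair the text. Even with a cut-off reading, a person with an entry by that date is not unvaccinated, and no sentence puts such people back in the reference group.

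Matching on calendar week equalises the time left in the wave. It does not remove a difference in uptake after the result within a week. Conditional logistic regression uses the same groups.

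Other objections stand and limit the point:

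- A reader might infer that controls are necessarily removed more than cases, so that every absolute VE is inflated. The article does not say that vaccination was deferred after infection, and gives no uptake by test result. Equal uptake gives no bias, and higher uptake in cases reverses it.
- A reader might infer that the shift always exceeds the planned precision. At higher VE it often does not, as shown above.
- A reader might infer that the waning analysis is distorted. Time bands within a wave share one reference group, so a common factor cancels from ratios between them. A week-varying loss that survives matching and adjustment has not been shown.
- The assumed f need not suit both waves. The article places the introduction of four vaccines in August 2021, inside the Delta period, which makes later first doses likely there. By the Omicron period the rollout was about a year old, and f may be smaller.

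**Conclusion.** The definition is wrong as written and the sections contradict each other: unvaccinated status is fixed at the end of the wave, dose status before the index test, and the objective speaks of status at the test. People first dosed between the test and the end of the wave have no exposure class.

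For death, a secondary outcome, the direction follows by logic: VE is inflated whenever some unvaccinated comparators are vaccinated later. With an assumed 20–40% of comparators lost, a true 50% reads 60–70%. For symptomatic infection, the primary outcome, the direction is conditional: upward if f_control exceeds f_case, which is plausible but undocumented, nil if they are equal, and downward otherwise. Under the assumed 20%/5% to 40%/10%, a true 50% reads 58–67%, 70% reads 75–80% and 90% reads 92–93%. The shift can exceed the planned ±5 points at lower VE, but not at 90% under these assumptions. Relative VE is largely unaffected.

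The fault in the definition is certain. The size is not, because every f is assumed. Since the rule builds the reference group for the primary analysis and correcting it is nearly free, it should be corrected before VE is estimated.

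**What to change.** Define exposure for everyone at the index test date, with a single cut-off:

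- Unvaccinated: no PCARE Vaksin dose dated before the index test date, whatever happens later.
- Vaccinated: at least one dose dated before the index test date, classed by the last such dose.
- A dose given on the day of the test counts as no prior dose, so nobody is left without a class.

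In Study Variables, remove the end of the period as a classification date. In Data Sources, add the same date condition to the sentence that makes linked people vaccinated. Align both with the secondary objective. Report, by case status and by wave, how many people this returns to the reference group; that also gives the actual f_case and f_control. With everyone classified at the test, the multiplier is 1.

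The cost is a few words in two sections and a recode of the linked file. Table 1 lists vaccination date among the PCARE Vaksin variables, so no new data are needed. The reported VE may become less favourable.
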